## Abstract

**Background:**

Latin America, China and India are experiencing unprecedentedly rapid demographic ageing with an increasing number of people with dementia. The 10/66 Dementia Research Group's title refers to the 66% of people with dementia that live in developing countries and the less than one tenth of population-based research carried out in those settings. This paper describes the protocols for the 10/66 population-based and intervention studies that aim to redress this imbalance.

**Methods/design:**

Cross-sectional comprehensive one phase surveys have been conducted of all residents aged 65 and over of geographically defined catchment areas in ten low and middle income countries (India, China, Nigeria, Cuba, Dominican Republic, Brazil, Venezuela, Mexico, Peru and Argentina), with a sample size of between 1000 and 3000 (generally 2000). Each of the studies uses the same core minimum data set with cross-culturally validated assessments (dementia diagnosis and subtypes, mental disorders, physical health, anthropometry, demographics, extensive non communicable disease risk factor questionnaires, disability/functioning, health service utilisation, care arrangements and caregiver strain). Nested within the population based studies is a randomised controlled trial of a caregiver intervention for people with dementia and their families (ISRCTN41039907; ISRCTN41062011; ISRCTN95135433; ISRCTN66355402; ISRCTN93378627; ISRCTN94921815). A follow up of 2.5 to 3.5 years will be conducted in 7 countries (China, Cuba, Dominican Republic, Venezuela, Mexico, Peru and Argentina) to assess risk factors for incident dementia, stroke and all cause and cause-specific mortality; verbal autopsy will be used to identify causes of death.

**Discussion:**

The 10/66 DRG baseline population-based studies are nearly complete. The incidence phase will be completed in 2009. All investigators are committed to establish an anonymised file sharing archive with monitored public access. Our aim is to create an evidence base to empower advocacy, raise awareness about dementia, and ensure that the health and social care needs of older people are anticipated and met.

## Background

### The 10/66 dementia research group

The title of the 10/66 Dementia Research Group [1-4] refers to the 66% of people with dementia that live in developing countries and the less than one tenth of population-based research carried out in those settings. We have attempted to redress the research imbalance through south-south and south-north research collaborations. Our first symposium in Cochin in 1998 established clear priorities [1], which have guided our subsequent research programme.

**1) Methodological problems needed first to be addressed**, particularly development of culture- and -education fair dementia diagnostic procedures, a prerequisite for meaningful comparison between regions [2]. Our pilot studies in 26 centres in Latin America and the Caribbean, Africa, India, Russia, China and SE Asia demonstrated the feasibility and validity of a one stage culture and education-fair diagnostic protocol for population-based research [5,6], the resulting '10/66 Dementia' outcome being derived from a probabilistic algorithm.

**2) More research was needed to describe dementia prevalence and incidence**. Local evidence of numbers of people affected, and associated burden would raise awareness and inform policymaking. Regional variations in disease frequency could give clues regarding aetiology, if obtained using harmonised and cross-culturally valid methods.

**3) Description of care arrangements for people with dementia**. In our pilot studies we showed that levels of caregiver strain, among caregivers of people with dementia are at least as high as those typically reported from developed countries, despite the strong traditions of extended family care in most of the countries studied [7-9]. We have also highlighted the lack of awareness and understanding of the nature of the dementia syndrome, and the unresponsiveness of health care services as currently constituted [8,10,11]. Behavioural symptoms, such as agitation, wandering, calling out repeatedly, are common in developing countries, associated with stigma and blame, and an important source of distress for caregivers [12].

**4) The effectiveness of new services for people with dementia and their caregivers**. We have shown that community health workers in Brazil [13] and India [14] can, after one day of training, identify cases of dementia in the community with reasonable accuracy using their knowledge of older people from their outreach work (which focuses mainly on maternal and child health). We have gone on to develop a simple five session caregiver education and training intervention, suitable for administration by a community health worker.

Since the pilot phase (1999–2001), the 10/66 DRG has conducted population-based surveys of dementia prevalence and impact in 14 catchment areas in 10 low and middle income countries (2003–2007). Nested within the population-based studies is a randomized controlled trial of a caregiver intervention for people with dementia and their families. We will shortly embark on an incidence phase with a 2.5 to three year follow-up of baseline participants in seven of the 10 countries (2007–2010). The purpose of this paper is to describe the protocols for the three elements of the research programme; the baseline survey, the incidence phase, the casefinder approach and the randomized controlled trial; and in doing so, publicize the publicly accessible 10/66 data archive that will be established by the following centres: India (Vellore and Chennai), Nigeria, China, Cuba, the Dominican Republic, Venezuela, Mexico, Peru and Argentina. The Brazilian centre will establish an independent data archive.

### The demographic and health transitions

Demographic ageing proceeds apace in all world regions, more rapidly than first anticipated [15]. The proportion of older people increases as mortality falls and life expectancy increases. Population growth slows as fertility declines to replacement levels. Latin America, China and India are experiencing unprecedentedly rapid demographic ageing (Figures 1 and 2).

**Figure 1 F1:**
[figure not shown]
Global demographic ageing, 2000–2050 (UNDIESA).

**Figure 2 F2:**
[figure not shown]
Demographic transition, UK and China.

In the accompanying health transition non-communicable diseases (NCD) assume a progressively greater significance in low and middle income countries (LAMIC). NCDs are already the leading cause of death in all world regions apart from sub-Saharan Africa. Of the 35 million deaths in 2005 from NCDs, 80% will have been in LAMIC [16]. This is partly because most of the world's older people live in these regions – 60% now rising to 80% by 2050. However, changing patterns of risk exposure also contribute. Latin America exemplifies the third stage of health transition. As life expectancy improves, and high fat diets, cigarette smoking and sedentary lifestyles become more common, so CVDs have maximum public health salience – more so than in stage 2 regions (China and India) where risk exposure is not yet so elevated, and in stage 4 regions (Europe) where public health measures reduced exposure levels [17]. The INTERHEART cross-national case-control study suggests that risk factors for myocardial infarction operate equivalently in all world regions, including Latin America and China [18].

### Dementia in developing countries

#### Global burden

It has been recently estimated that 24.2 million people live with dementia worldwide (based upon systematic review of prevalence data and expert consensus), with 4.6 million new cases annually [19] (similar to the annual global incidence of non-fatal stroke [20]). Most people with dementia live in LAMIC, 60% in 2001 rising to 71% by 2040. Numbers will double every twenty years to over 80 millions by 2040. Increases to 2040 will be much sharper in developing (300%) than developed regions (100%). Growth in Latin America will exceed that in any other world region. Well designed epidemiological research can generate awareness, inform policy, and encourage service development. However, such evidence is lacking in many world regions, and patchy in others, with few studies and widely varying estimates [19]. There is a particular dearth of published epidemiological studies in Latin America with two descriptive studies only, from Brazil [21,22] and Colombia[23].

#### Developed/developing country differences

Prevalence of dementia is somewhat lower in developing countries than in the developed north [2], strikingly so in some studies [24,25]. Our expert consensus panel, reviewing all available evidence, confirmed this trend [19], which seems not to be explained by differences in survival[25,26]. Mild dementia may be under-detected because of difficulties in establishing the criterion of social impairment. Differences in levels of exposure to environmental risk factors may also have contributed, with low levels of cardiovascular risk [27] and hypolipidaemia [28,29] in some developing countries suggested as explanations. Other potential risk exposures will be more prevalent in LAMIC, for example anaemia associated with AD in rural India [30]. Dietary deficiencies, particularly of micronutrients, are widespread and strongly linked to poverty. Deficiencies of folate and vitamin B_12 _are of particular interest given their consequences; anaemia, neuropathy, hyperhomocysteinaemia [31], increased risk of stroke and IHD [32]. Vitamin B_12 _deficiency is strikingly prevalent (> 40%) across Latin America [33-35], linked to gastrointestinal infections and diets deficient in meat and dairy produce [33]. Folate deficiency is endemic in those living in poverty [34], and after economic crisis [35]. Diets deficient in legumes may have contributed. Micronutrient deficiency is probably more prevalent in the elderly but there are few data on this age group [33]. Iodine deficiency has also been a major public health problem in most Latin American countries [36]. Iodized salt is now generally available but iodine content is poorly regulated [36]. We found only one study from the region, reporting a prevalence of sub-clinical hypothyroidism of 16.1% in post-menopausal Brazilian women [37]. High infant mortality may contribute to population differences in dementia frequency; constitutional and genetic factors that confer survival advantage in early years may protect against neurodegeneration or delay its clinical manifestations. According to this model, current dementia frequency in developing countries would correlate inversely with infant mortality at the time that those at risk were born. In 1948, infant mortality in the UK was 38/1000 live births compared with 207 in Nigeria, 195 in China and 190/1000 in India. Infant mortality in Latin America varied from 40/1000 in Cuba, to 70 in Argentina, 81 in the Dominican Republic, 98 in Venezuela, 102 in Mexico, 109 in Peru and 135/1000 in Brazil. [38]. It seems plausible that as patterns of morbidity and mortality converge with those of the developed west, then dementia prevalence will do likewise [39].

### Dementia aetiology

#### Dementia, cardiovascular risk factors and cardiovascular disease

Recent research suggests that vascular disease predisposes to AD as well as to vascular dementia [40]. In short [41-43] and longer latency [44,45] incidence studies, smoking increases the risk for Alzheimer's disease. Inverse associations from case-control studies are thought to be explained by prevalence-incidence bias, with smoking influencing dementia-specific mortality [46]. Diabetes is also a risk factor [47], and in longer term cohort studies, midlife hypertension [48,49] and hypercholesterolemia [49] are associated with AD onset in later life. Aggregated cardiovascular risk indices incorporating hypertension, diabetes, hypercholesterolaemia and smoking incrementally increase risk for dementia incidence whether exposure is measured in midlife [45] or a few years before dementia onset [43]. Recent studies report associations between metabolic syndrome and incident cognitive decline [50], and insulin resistance and impaired executive function [51], but the role of the metabolic syndrome is as yet little explored. Despite occasional negative findings from large prospective studies [52,53], the accumulated evidence for a causal role for CVRF and CVD in the aetiology of dementia and AD is very strong. This has led to the hypothesis that atherosclerosis and AD are convergent disease processes [54], with some common pathophysiological and aetiologic factors (APOE e4 polymorphism, hypercholesterolaemia, hypertension, hyperhomocysteinaemia, diabetes, metabolic syndrome, smoking, systemic inflammation, increased fat intake and obesity).

#### Nutritional factors

Our review of the literature suggests two areas, of particular relevance to LAMICs, needing more research.

a) Research on micronutrients and dementia in developed countries has focussed upon antioxidants [55] with less attention towards deficiencies in vitamin B_12 _and folate, which result in hyperhomocysteinaemia; only four small incidence studies [56-59], all underpowered and with inconsistent findings. Two out of three studies testing for an effect of folate were positive [56,57], in one case independent of homocysteine [56]. B_12 _was associated in only one out of four studies [57].

b) Overt hypothyroidism is a potentially reversible cause of dementia. Sub-clinical hypothyroidism (raised TSH levels with normal T4) is more prevalent, affecting up to 20% of older people in developed countries. It is associated with elevated total cholesterol and progression to overt hypothyroid disease, possibly also CVD [60]. It was strongly associated with risk for dementia in one cross-sectional study [61]. Conversely, a small incidence study reported a strong association with sub-clinical hyperthyroidism (low TSH) [62].

### Ethnic differences and research in admixed populations

Previous research indicates strong and consistent ethnic differences in the incidence of dementia and stroke, in shared risk factors for atherosclerosis and dementia (lipid metabolism, hypertension, metabolic syndrome, APOE genotype), and in risk associations between certain of these risk factors and these outcomes.

#### Dementia

The age-specific prevalence [25] and incidence[26] of dementia in Nigeria are both very low. A further notable finding is the apparent lack of an association between APOE genotype and dementia [63], confirmed in Kenya [64]. Those with African ancestry tend to have a higher prevalence of APOE e4, but African Americans, other populations of west African ancestry, and Hispanics, all show weak and inconsistent associations with AD [65]. There is a robust association between APOE genotype and AD in Europeans and south Asians [66].

#### Stroke, heart disease and CVD risk factors

In the South London Stroke study [67] age and sex adjusted stroke incidence was higher among black (African Caribbean) residents, with a RR of 2.2 (1.8–2.8). In the USA incidence was higher among African Americans and Hispanics [68,69]. These differences may be partly explained by elevated blood pressure levels [70]. In the North Manhattan Stroke Project, both relative risks and population attributable fractions varied across white, black and Hispanic ethnic groups for the major stroke risk factors [71]. Conversely, African Caribbean migrants in the UK have a low risk of heart disease despite a high prevalence of metabolic syndrome, an effect attributed to a low prevalence of smoking and low triglyceride levels [70].

#### Admixture proportions

Measurement of individual admixture proportions (the proportions of the individual's genome that are of African, European, and Native American ancestry) is important for three reasons.

1. Studying the relationship of disease risk to admixture proportions is the most direct way to distinguish genetic from environmental explanations for ethnic variation in disease risk [72].

2. Such relationships will confound studies of any other genetic or environmental risk factors – "hidden population stratification". Measurement of the confounder allows us to control for it by standard methods.

3. Genes underlying ethnic variation in disease risk may be localized by admixture mapping, exploiting information about linkage generated by admixture [73].

## Aims of the 10/66 population-based research programme

### Primary objectives

1. To create a publicly accessible data archive from the 10/66 Dementia Research Group's cross-sectional population-based surveys including over 17,000 older people from six countries in Latin America and the Caribbean, India, China and Nigeria.

2. To use these data for comparative descriptive analyses of dementia prevalence, and its associated impact including: the economic costs of illness in each centre comprising indirect (informal care) costs, lost earnings and direct costs (health and social care and medication); the relative independent contribution of dementia and other major non-communicable disorders to direct and indirect costs, disability, dependency and caregiver strain.

3. To model dementia prevalence, examining the effects of age, education, literacy and SES, and at population level of urban vs. rural setting, historical levels of infant mortality, economic development, and industrialization.

4. To conduct a 2.5 to three year incidence phase follow-up of the baseline sample. The incidence phase will exploit the particularly rich baseline cross-sectional data in the six Latin American countries (Cuba, Dominican Republic, Venezuela, Mexico, Peru and Argentina) and in China, aiming:

5. To estimate the annual incidence rate of dementia and its subtypes, by age group, education and centre, and to investigate risk factors for incident dementia and AD, testing the following specific hypotheses: a) cardiovascular risk factors (diabetes, hypertension, large waist circumference, high waist hip ratio, hypercholesterolaemia, hypertriglyceridaemia, metabolic syndrome and smoking) and stroke increase the risk for incident dementia and AD, after controlling for confounding effects. Associations will be quantified as relative risks and population attributable fractions; b) micronutrient deficiencies (vitamin B_12 _and folate), and anaemia increase the risk for incident dementia and AD, and mediate any effect on these outcomes of overall nutritional deficiency; c) sub-clinical hypothyroidism is associated with increased risk of dementia and AD; d) incident dementia and AD are inversely associated with the proportion of the genome that is of African ancestry, and the association between APOE e4 genotype and incident dementia and AD is modified by admixture proportions – weaker in those with least African ancestry.

6. To confirm the predictive validity of the survey dementia diagnoses (DSM IV and 'the 10/66 dementia algorithm') and Mild Cognitive Impairment (MCI) through three year follow-up of all dementia and MCI cases. This will include a longitudinal study of evolving care arrangements and caregiver strain.

### Secondary objectives

#### 1. Mortality

a) to estimate annual all-cause and cause-specific mortality in each incidence centre; b) To investigate the independent effects upon all-cause and cardiovascular mortality of education, socio-economic status, cardiovascular risk factors (CVRF), prevalent cardiovascular disease (CVD), dementia, cognitive impairment, and depression

#### 2. Stroke

a) to estimate, in the same centres the annual attack rates for stroke; b) to compare the risk factor profile for incident stroke (relative risks and population attributable risk fractions) between centres and within centres between men and women and better and less well educated participants.

#### 3. Depression

To study the social aetiology of late-life depression cross-sectionally in all ten centres, and prospectively in the incidence centres including the effects of relative and absolute poverty, ill health and disability, nutritional status, social support, life events, marital circumstances and living arrangements.

#### Settings

Ten low and middle income countries (India, China, Nigeria, Cuba, Dominican Republic, Brazil, Venezuela, Mexico, Peru and Argentina). China, India, Peru and Mexico recruited from separate urban and rural catchment areas; the other centres included urban catchment areas only.

#### Catchment areas and sample registration

For urban catchment areas predominantly middle-class or professional areas with high-income earners were avoided. Rural catchment areas were defined by low population density, and traditional agrarian lifestyle. Catchment area boundaries were precisely defined. Mapping was carried out to identify and locate all households, which were allocated household IDs. Households were enumerated to identify possible eligibles (aged 65 and over). Age (and therefore eligibility) was formally determined on revisit for interview. For each household the genders and ages of all usual residents was recorded with the names of those aged 65 years or over on the census date. Household and participant details were stored in secure databases. These contained names, addresses, ID numbers, and contact details for neighbours, key informants and friends to facilitate tracing for potential follow-up. Precision calculations indicated that an overall sample of 2,000 would allow estimation of a typical dementia prevalence of 4.5% with a precision of +/- 0.9%. Rural and urban samples of 1,000 each will allow estimation of the same prevalence with a precision of +/- 1.2%.

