##### 1) Outcome – The diagnosis of dementia

Our previously published 10/66 dementia diagnosis algorithm [5] requires

(i) A structured clinical mental state interview, the Geriatric Mental State, which applies a computer algorithm (AGECAT)[74], identifying organicity (probable dementia), depression, anxiety and psychosis and,

(ii) A cognitive test battery comprising a) the Community Screening Instrument for Dementia (CSI'D') COGSCORE [75] (incorporating the CERAD animal naming verbal fluency task), and b) the modified CERAD 10 word list learning task with delayed recall [76] and

(iii) An informant interview the CSI'D' RELSCORE [75], for evidence of cognitive and functional decline

(iv) an extended informant interview, the History and Aetiology Schedule – Dementia Diagnosis and Subtype (HAS-DDS), a modification of the earlier HAS [77], providing more detailed information on onset and course of a possible dementia syndrome

v) The NEUROEX, a brief fully structured neurological assessment with objectified quantifiable measures of lateralising signs, parkinsonism, ataxia, apraxia and primitive 'release' reflexes [78,79].

(vi) Behavioural and Psychological symptoms of dementia (BPSD); assessed using an informant questionnaire, the Neuropsychiatric Inventory (NPI-Q) [80].

Final dementia diagnoses is made in two ways. The main dementia outcome is defined as those scoring above a cutpoint of predicted probability of DSM IV Dementia syndrome [81] from the logistic regression equation developed in the 10/66 international pilot study, using coefficients from the GMS, CSI-D and 10 word list learning tasks [5]. The second approach involves the direct application of research diagnostic criteria for DSM IV and for the following dementia subtype diagnoses; NINCDS-ADRDA Alzheimer's disease criteria [82], NINDS-AIREN vascular dementia criteria [83], and Lewy Body Dementia [84]. The clinical assessment identifies other prevalent conditions relevant to the differential diagnosis of dementia and dementia sub-type: psychosis, depression, anxiety disorder, alcoholism, epilepsy and stroke. Circularity in further validation of these diagnoses can only be avoided by focusing upon their predictive validity. Thus, a diagnosis of dementia should lead to further cognitive and functional decline, and not recovery.

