#### Power and sample size considerations

Power estimations were carried out using Stata 8.2 ssmenu command [100] for sample size and power calculations in complex studies with failure time outcomes (table 2). Pooling the data across the six Latin American centres yields the following power (Table 3) for identification of the following effect sizes for associations with incident dementia and stroke, assuming the following prevalences of risk exposure.

**Table 2 T2:** Incident dementia, stroke and all-cause mortality in centres participating in the follow-up study

Country	Baseline sample	Dementia at baseline	Free of dementia at baseline	Available for FU interview^1^	Person years	Deaths	Incident dementia^2^	Incident strokes
Cuba	3000	330	2670	1994	6730	509	55	45
DR	2000	220	1780	1329	4488	339	37	30
Venezuela	2000	200	1800	1345	4490	339	37	30
Mexico	2000	200	1800	1381	2906	295	30	25
Peru	2000	200	1800	1381	2906	295	30	25
Argentina	2000	200	1800	1381	2906	295	30	25
Sub-total^3^	13000	1350	11650	8811	24426	2072	219	180
China	2162	137	2025	1513	5105	366	42	30
TOTAL	15000	1300	11700	10324	29531	2438	261	210

1. assuming 6% annual mortality (GBD 2002 AMRO B mortality data, 65 and over), and 15% non-response/non-traceability.

2. annual incidence rate of 0.0092 for all those aged 65 and over, from consensus prevalence estimates for Latin America [19], using DISMOD to derive incidence from prevalence and survival.

3. These centres included fasting blood samples, which are lacking in China

**Table 3 T3:** Power to detect given effect sizes (HRs) for associations between exposures with a prevalence of 10% and 20%, for the outcomes of dementia and stroke.

Minimum Hazard Ratio to be detected	Power for detecting association with 10% exposure prevalence		Power for detecting an association with 20% exposure prevalence	
Outcome^1,2^	Dementia	Stroke	Dementia	Stroke

2.5	100%	99.8%	100%	100%
2.0	96.4%	90.9%	99.8%	98.8%
1.8	86.0%	75.8%	97.5%	92.8%
1.5	48.8%	39.3%	71.0%	59.5%

1. The power to detect associations with all-cause mortality approximates to 100% in each of these cells

2. As approximately 70% of dementia cases are categorised as AD, the power of detecting given associations with this outcome is very similar to that for stroke.

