The 10/66 dementia diagnosis has been carefully validated across all of the cultures, and in each of the centres in which the population research is proceeding. While sensitivity (94%) and specificity (97% in high education controls and 94% in low education controls), against the gold standard of a local clinician's DSM IV diagnosis were both excellent, the false positive rate which varied between 1% and 10% across regions and levels of education can be expected to result in a higher prevalence of 10/66 dementia, compared with that of DSM IV dementia. DSMIV criteria are recognized to be relatively restrictive. Impairment is required in memory and other specified domains of function. Each of these must have progressed, and led to social or occupational impairment. The deficits should not be explained by delirium or other mental disorder. The aim with DSMIV (and other similar diagnostic criteria) was to define a progressive and relatively pervasive disorder with thresholds set high to maximize reliability between raters and centres. Clinically relevant dementia may therefore be prevalent beyond the confines of the narrowly defined DSM IV criterion. One of the few population-based studies to examine this issue directly, the Canadian Study of Health and Aging [107] reported a prevalence of 20.9% for those aged 65 and over according to clinical consensus compared with 13.7% according to DSM IV criterion. Mild cases, confirmed by clinicians, were selectively excluded by the DSM IV criterion. None of the DSM IV criteria are specifically required by the 10/66 probabilistic algorithm, which simply requires a profile of cognitive impairment on formal testing, informant reports of cognitive and functional decline, and findings on clinical interview that are consistent with a high probability of being a case. While the DSMIV algorithm identifies clear cut, severe and pervasive dementia cases, the 10/66 algorithm may be more relevant to establishing the true population burden of the dementia syndrome.

The catchment area sampling strategy enables us to foster links within each local community, improving response and facilitating possible follow-up. Community sensitisation proved to be essential to ensure a good response to the surveys. Prevalence estimates and other descriptive elements may not generalize beyond these and similar communities, but this is unlikely to lead to bias in estimates of association.

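### Survey precision is stated at a 4.5% dementia prevalence that Table 2 does not share (10-11% in Latin America, 6.3% in China), and the ±1.2% for samples of 1,000 should be ±1.3% even at 4.5%

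*Protocol article*

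**What the plan says.** Under Catchment areas and sample registration, the article states that "an overall sample of 2,000 would allow estimation of a typical dementia prevalence of 4.5% with a precision of +/- 0.9" per cent. It adds: "Rural and urban samples of 1,000 each will allow estimation of the same prevalence with a precision of +/- 1.2" per cent. The casefinder study uses the same rate, expecting about 90 cases among 2,000 people (90/2,000 = 4.5%).

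Table 2, under Power and sample size considerations, uses other rates. It removes people with dementia at baseline to reach the cohort at risk. Its rows begin "Cuba 3000 330 2670" and "DR 2000 220 1780"; Venezuela, Mexico, Peru and Argentina each have 200 of 2,000, and China 137 of 2,162.

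On case definition, the outcome section says: "The main dementia outcome is defined as those scoring above a cutpoint of predicted probability of DSM IV Dementia syndrome". That is the 10/66 algorithm; direct application of DSM IV criteria is the second approach. The Methodological issues section says that the algorithm's false positives "can be expected to result in a higher prevalence of 10/66 dementia, compared with that of DSM IV dementia". Neither the 4.5% nor the Table 2 column is labelled with a definition.

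**The concern.** One article plans on two baseline prevalences that differ by more than a factor of two in Latin America. The half-width of a prevalence estimate depends on the prevalence, so a precision quoted at 4.5% does not carry over to a centre where the article itself expects 10-11%. Comparative prevalence and the urban-rural contrast are among the primary objectives (2 and 3), so readers will use these figures to judge what the surveys can show. The figure for samples of 1,000 also appears too small on its own terms.

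**Working it through.** **Inputs.** Prevalence 4.5%, with n = 2,000 and 1,000 (Catchment areas and sample registration). Table 2 prevalences: Cuba 330/3,000 = 11.0%; Dominican Republic 220/2,000 = 11.0%; Venezuela, Mexico, Peru and Argentina 200/2,000 = 10.0% each; Latin American sub-total 1,350/13,000 = 10.4%; China 137/2,162 = 6.3%. The confidence level is not stated. I assume 95%, simple random sampling, and no design effect or finite-population correction.

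**Formula.** Half-width = 1.96 × √(p(1−p)/n).

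**Step 1: the plan's own figures.**
- n = 2,000: 1.96 × √(0.045 × 0.955/2,000) = 0.909%. The stated ±0.9% is reproduced.
- n = 1,000: 1.96 × √(0.045 × 0.955/1,000) = 1.285%, which rounds to 1.3%. The stated ±1.2% is not reproduced.
- Other methods at n = 1,000: the Wilson interval gives 1.294% and a 90% interval gives 1.078%. The exact (Clopper-Pearson) interval gives −1.20/+1.47, so only its lower arm matches.

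**Step 2: the same formula at the Table 2 prevalences.**

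| Prevalence | n = 2,000 | n = 1,000 |
|---|---|---|
| 4.5% (stated) | 0.91% | 1.285% |
| 6.3% (China) | 1.07% | 1.51% |
| 10.0% | 1.31% | 1.86% |
| 11.0% | 1.37% | 1.94% |

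Cuba has n = 3,000 at 11%, which gives 1.12%.

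**Step 3: size of the gap against the printed figures.**
- n = 2,000: 1.31/0.9 = 1.46 and 1.37/0.9 = 1.52.
- n = 1,000: 1.86/1.2 = 1.55 and 1.94/1.2 = 1.62.

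The half-widths are therefore about 45-60% wider than stated for Latin American samples of nominal size. At n = 1,000 part of this is the slip in Step 1: against 1.285% the ratios are 1.45 and 1.51.

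**Step 4: relative precision.** At n = 2,000 the half-width as a share of the estimate is 0.909/4.5 = 20% at 4.5%, 1.31/10 = 13% at 10% and 1.37/11 = 12.5% at 11%. It improves.

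**Step 5: rural areas below 1,000.** Table 1 sets targets of 500 in Canete (569 completed) and 800 in Canuelas (800 completed). With n = 569 the half-width is 1.70% at 4.5% and 2.47% at 10%. With n = 800 it is 1.44% and 2.08%.

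**The case against.** The strongest reply is that the precision statement is conditional. It gives a half-width at 4.5%, not at 10%, and for 2,000 people that half-width is correct. This stands. A reader might infer that the article promises a precision for its main outcome and fails to deliver it, but no such promise is made. Only the ±1.2% is an arithmetic error, of about 0.09 percentage points.

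A reader might also infer that Table 2 counts cases under the 10/66 algorithm while 4.5% is a DSM IV figure. This is plausible. If DSM IV prevalence were 4.5% (an assumption), the article's sensitivity of 94% and specificity of 94-97% would imply a 10/66 prevalence of 0.94 × 4.5% + (3% to 6%) × 95.5% = 7.1% to 10.0%. The documents do not confirm it, however: the Table 2 column names no definition and nothing labels the 4.5%. Table 2 is also at least partly projected. It gives Argentina 200 cases among 2,000, while Table 1 shows no completed interviews in Buenos Aires and 800 in Canuelas. Its figures cannot all be read as observed counts.

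The 10-11% is not general either. China is at 6.3%, and India, Nigeria and Brazil are not in Table 2. Cuba's larger sample offsets most of the widening.

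Finally, a reader might conclude that these samples cannot resolve urban-rural or between-country differences. That does not follow. For absolute differences between two areas of 1,000, the half-width does grow, from √2 × 1.285 = 1.8 to √2 × 1.86 = 2.6 points. For a prevalence ratio of 1.5, however, power rises from about 59% (4.5% v 6.75%) to about 92% (10% v 15%). The article makes no claim about detecting such differences in prevalence.

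What the objection leaves standing is the wrong ±1.2% and two unreconciled prevalences in one plan.

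**Conclusion.** The point holds as a wrong figure and an unreconciled input. The ±1.2% for samples of 1,000 should be ±1.3% at the article's own 4.5%. That 4.5%, used for survey precision and implied in the casefinder study, conflicts with the rates that Table 2 enters for every centre it covers. At those rates the stated absolute precision is missed at the nominal sizes, by about 45-60% in Latin America and less in China. The ±0.9% is correct as stated, and the widening does not make the surveys inadequate. The sizes rest on 95% confidence and simple random sampling; clustering within households or areas would usually widen all the intervals. The surveys are nearly complete, and reported intervals will come from the data. The consequence is therefore limited to what readers are led to expect.

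**What to change.** Change the text only; no extra enrolment is needed.

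1. Correct ±1.2% to ±1.3% for samples of 1,000 at 4.5%, and state the confidence level.
2. Reconcile the 4.5% in the catchment-area section and the casefinder study with Table 2, and name the case definition behind each. Do not label the 4.5% as DSM IV unless the sponsor confirms it. Say which Table 2 entries are projected.
3. Add the half-widths at the Table 2 prevalences: ±1.3-1.4% (n = 2,000) and ±1.9% (n = 1,000) at 10-11%; ±1.1% for Cuba (n = 3,000); ±1.1% and ±1.5% at 6.3%. Note that Canete and Canuelas, with targets below 1,000, have wider intervals.

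The cost is a few sentences and a less favourable stated absolute precision. If the casefinder prevalence is revised to 10%, its expected cases rise from about 90 to 200 per 2,000, which favours that study.
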